### 2.5. Measures

Participants in both the control/waiting-list and VR/experimental groups will fill in the same screening and outcome measures.

#### 2.5.1. Screening Measures

All participants who will provide written informed consent and meet the criteria to be included in the experimental part of the study will be asked to fill in the following questionnaires:−A non-psychometric self-report questionnaire to collect socio-demographic (age, marital status, educational level, and occupational status) and clinical data (body mass index (BMI), former DSM-5-TR diagnosis, and clinical conditions and/or use of medical devices interfering with VR) and to investigate the participants’ familiarity with the use of a computer or technological devices (i.e., computer and videogames) in their everyday life.−The Alcohol Use Disorders Identification Test (AUDIT) [38] is a 10-item psychometric screening tool developed by the World Health Organization (WHO) to assess alcohol consumption, drinking behaviors, and alcohol-related problems. AUDIT scores higher than five indicate a potentially harmful pattern of drinking, with a sensitivity of 0.84 and a specificity of 0.90 in the Italian population [39].−The Fagerström Test for Nicotine Dependence (FTND) [40,41] is a 6-item self-report psychometric instrument for assessing the intensity of physical addiction to nicotine in terms of the quantity of cigarette consumption, compulsion to use, and dependence. Scores between three and four at the FTND indicate a low-to-moderate dependence, scores between five and seven indicate a moderate dependence, and scores higher than eight indicate a high dependence. The Italian version of the FTND showed low internal consistency reliability, with a Cronbach’s alpha of 0.55 in the combined sample (=0.59 among men and =0.50 among women) [41].−The Eating Disorders Examination Questionnaire (EDE-Q 6.0) [42,43] is a 28-item psychometric self-report questionnaire to evaluate their levels of ED psychopathology. The EDE-Q focuses on the past 28 days and produces a global score as well as four subscales: Eating Concern, Shape Concern, Weight Concern, and Restraint. The EDE-Q also includes items measuring the frequency of core ED behaviors, such as binge eating and compensatory behaviors. Higher scores are indicative of higher eating pathology, and scores between 1.56 and 3.91 are found to be associated with ED risk in the GP [44]. The EDE-Q demonstrated satisfactory concurrent validity [42,43] and acceptable internal consistency (Cronbach’s α ranging from 0.70 to 0.83 for the subscale and ≥0.90 for the global score) [45].

Participants will be selected to participate in the intervention phase if they score at least 5 on the AUDIT, 7 on the FTND, or 1.56 on the EDE-Q and assigned to the respective group, according to the displayed dysfunctional behavior.

#### 2.5.2. Outcome Measures

Changes in the levels of endorsed unhealthy behaviors will be measured by administering the FTND, AUDIT, SCOFF, and EDE-Q at the beginning (T0) and end (T1) of the VR intervention to the participants of the relative sample, as well as at the 3- (T2) and 6-month (T3) follow-up.

The following instruments will instead be administered to participants of all samples at T0, T1, T2, and T3 to evaluate their levels in the three considered transdiagnostic factors (i.e., emotion regulation, experiential avoidance, and psychological flexibility) as well as participants’ levels of stress:−The Difficulties in Emotion Regulation Scale-brief version (DERS-16) [46], which is a 16-item self-report psychometric questionnaire evaluating six ER strategies: 1. non-acceptance of emotional responses, 2. difficulty in engaging in goal-directed behaviors, 3. impulse control difficulties, 4. lack of emotional awareness, 5. limited access to ER strategies, and 6. a lack of emotional clarity. DERS-16 reported good test–retest reliability [46] and excellent internal consistency (Cronbach’s alphas between 0.87 and 0.96) [47]. The DERS-16 scores were also found to strongly correlate with levels of psychological distress in clinical and non-clinical populations [46,48,49,50].−The Acceptance and Action Questionnaire-II (AAQ-II) [51,52] is a 7-item self-report psychometric questionnaire assessing psychological flexibility. The Italian version of the AAQ-II proved to be a reliable and valid measure of psychological inflexibility, with high internal consistency (0.83) and modest test–retest reliability over a 12-month period (0.61) [51].−The Experiential Avoidance Scale (MPFI-EA) from the Multidimensional Psychological Flexibility Inventory (MPFI) [53,54], which is a 5-item self-report psychometric scale evaluating experiential avoidance taken from the MPFI, and a 60-item self-report questionnaire assessing global psychological flexibility and inflexibility processes. MPFI-EA showed high reliability in the Italian version (Cronbach’s alpha = 0.91) [53].−The Depression, Anxiety, and Stress Scale—21 (DASS-21) [55,56] is a 21-item self-report psychometric questionnaire designed to measure the emotional states of depression, anxiety, and stress. Each of the three DASS-21 scales contains seven items that are divided into subscales. In particular, the stress scale is sensitive to the levels of chronic non-specific arousal. It assesses difficulty relaxing, nervous arousal, being easily upset/agitated, irritable/over-reactive, and impatience. Scores between 19 and 25 on the DASS-21 stress scale indicate moderate levels of severe levels of stress, scores between 26 and 33 indicate severe stress, and scores higher than 34 indicate extremely severe levels of stress. The Italian version of the DASS-21 demonstrated good internal reliability, with Cronbach’s alpha of 0.90 in the community sample (Cronbach’s alpha = 0.85 for the stress scale) [55].

### 2.6. Data Analyses

Data analyses will be performed using SPSS Statistic vrs.28. Data analyses will be performed separately for the three samples that are included in the study (i.e., individuals who engage in heavy smoking, heavy drinking, and dysfunctional eating behaviors).

Descriptive statistics will be run to analyze socio-demographics (age, marital status, educational level, and occupational status), clinical characteristics (BMI, former DSM-5-TR diagnosis, clinical conditions, and/or the use of medical devices interfering with VR), and mean FTND, AUDIT, SCOFF, and EDE-Q scores in the relative groups. The mean DERS-16, AAQ-II, MPFI-EA, and DASS-21-stress scale scores will also be calculated for all samples separately.

To test pre-intervention differences between the experimental and control groups (waiting-list condition) in each sample, Chi-squares will be performed on categorical variables, whereas ANOVAs will be performed on continuous variables.

To test the effects of the VR-based intervention, changes over time in the relevant unhealthy behavior (FTND, AUDIT, or SCOFF and EDE-Q scores), in transdiagnostic factors (DERS-16, AAQ-II, and MPFI-EA scores), and in stress levels (DASS-21-stress scale scores) will be assessed in the experimental group of the samples using a priori contrast analysis. In particular, we plan to compare each assessment time (T0, T1, T2, and T3) against each other. The percentage of drop-out cases will be calculated.

To test the efficacy of the VR-based intervention compared to the control (waiting-list) condition, changes between the experimental and control (waiting-list) groups of the samples in the relevant unhealthy behavior (FTND, AUDIT, and EDE-Q scores), in transdiagnostic factors (DERS-16, AAQ-II, and MPFI-EA scores), and in stress levels (DASS-21-stress scale scores) will be tested by performing repeated measure ANOVAs using time (T0, T1, T2, and T3) as a within-subject factor and group assignment (experimental/VR vs. control) as a between-subject factor. To control for Type 1 error in within-group mean contrasts, the Bonferroni correction will be applied.

Moreover, to also take into consideration the possible multivariate nature of the involved variables and the association between dysfunctional behaviors, transdiagnostic factors, and stress, we will perform repeated measures MANOVAs using time (T0, T1, T2, and T3) as a within-subject factor, group assignment (experimental/VR vs. control) as a between-subject factor, and questionnaire scores (one between FTND, AUDIT, or EDE-Q scores depending on the sample, as well as DERS-16, AAQ-II, and MPFI-EA for transdiagnostic factors and DASS-21 for stress) as five dependent variables.

MANCOVAs will also be performed to compare the mean levels of relevant unhealthy behavior (FTND, AUDIT, or SCOFF and EDE-Q scores), transdiagnostic factors (DERS-16, AAQ-II, and MPFI-EA scores), and stress levels (DASS-21-stress scale scores) of the experimental and control (waiting-list) groups of the samples at each assessment time (T1, T2, and T3), adjusting for any differences at T0 and age. In particular, three MANCOVAs will be run (one for T1 scores, one for T2 scores, and one for T3 scores) for each sample relative to the dysfunctional behaviors using group (VR or waiting-list) as an independent variable, questionnaire scores (one between FTND, AUDIT, or EDE-Q scores depending on the sample, the questionnaires DERS-16, AAQ-II, and MPFI-EA for transdiagnostic factors and the DASS-21 for stress) as five dependent variables, and scores at T0 and age as covariates.

All analyses will be performed following an Intention-To-Treat (ITT) approach in order to preserve the randomized design and provide a more conservative estimate of treatment effects.

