To fill this gap in the literature, researchers and clinicians (clinical psychologists and psychotherapists [name], [name], and [name] and psychiatrist and psychotherapist [name]) from the Department of Psychology of the University of Bologna designed a transdiagnostic VR software and intervention protocol (H.O.M.E.—How to Observe and Modify Emotions) to improve emotion regulation, experiential avoidance, and psychological flexibility in order to make them suitable for several clinical and non-clinical populations. The H.O.M.E. intervention was designed to be a six-session intervention protocol focusing on the assessment of emotions elicited by trigger cues present in the virtual environment (e.g., comfort foods, cigarettes, alcohol, etc.) and the tackling of these emotions through CBT-based exercises to enhance the aforementioned transdiagnostic factors.

In particular, this study presents the research protocol for a randomized controlled trial designed to evaluate the effects of H.O.M.E. VR-based intervention in ameliorating the frequency and severity of unhealthy behaviors (i.e., heavy smoking, heavy drinking, and dysfunctional eating behaviors) and three transdiagnostic factors (emotion regulation, experiential avoidance, and psychological flexibility) levels in individuals of the general population that are considered at risk for nicotine dependence, alcohol abuse, or eating disorders. These experimental groups will be compared to a waiting-list condition consisting of a 6-week duration with weekly phone check-ups. The hypotheses are that H.O.M.E. will prove to be effective in reducing the frequency and severity of unhealthy behaviors as well as improving the transdiagnostic factors, even when compared to the waiting-list condition.

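### Section 2.6 labels uncontrolled before-after contrasts in the VR arm as the test of the intervention's effects, alongside valid randomised analyses

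*Protocol article*

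**What the plan says.** Section 2.6 sets out two tests in consecutive paragraphs.

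- **VR arm alone.** The stated purpose is "To test the effects of the VR-based intervention, changes over time in the relevant unhealthy behavior", with the transdiagnostic factors and stress treated in the same way. The changes "will be assessed in the experimental group of the samples using a priori contrast analysis", and "we plan to compare each assessment time (T0, T1, T2, and T3) against each other". Multiplicity is handled thus: "To control for Type 1 error in within-group mean contrasts, the Bonferroni correction will be applied".
- **VR against waiting list.** "To test the efficacy of the VR-based intervention compared to the control (waiting-list) condition, changes between the experimental and control (waiting-list) groups" are tested by repeated-measures ANOVA with time and group as factors. The section then adds time-by-group MANOVAs, and MANCOVAs at T1, T2 and T3 adjusted for T0 scores and age.

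Nothing marks the VR-arm contrasts as descriptive or secondary. The Introduction has the same two-part shape: its hypothesis describes H.O.M.E. as "effective in reducing the frequency and severity of unhealthy behaviors as well as improving the transdiagnostic factors, even when compared to the waiting-list condition". The Abstract also lists change in each VR group separately from the difference between VR and waiting list.

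Section 2.5.1 admits people "if they score at least 5 on the AUDIT, 7 on the FTND, or 1.56 on the EDE-Q", and section 2.5.2 uses the same scales as outcomes. Section 2.3 places T0 immediately before the first session, as a separate administration after screening.

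**The concern.** The waiting-list arm exists to absorb what would have happened without VR. A contrast confined to the VR arm discards it. Controls also receive phone check-ups, so some contact effects are common to both arms and only the between-arm comparison removes them.

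The label is what makes this more than a table-layout matter. Change described within an arm is harmless. Change presented as a test of the intervention's effects, with p-values and a multiplicity correction, invites a causal reading that the contrast cannot support.

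The outcome lists add a smaller problem. SCOFF is in the VR-arm list, but the between-arm ANOVA covers changes "in the relevant unhealthy behavior (FTND, AUDIT, and EDE-Q scores" and leaves it out. In that pair of analyses SCOFF is judged only without control.

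**Working it through.** The plan gives no figure for the error rate of the VR-arm contrasts, so there is none to reproduce. The question is how often such a contrast is significant when VR does nothing.

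**Inputs from the protocol article**
- About 64 people per sample, two arms, 30% drop-out (section 2.2). With 1:1 allocation (assumed), 64/2 = 32 per arm, and 32 × 0.7 = 22.4, taken as 22 completers.
- Four assessment times, all pairs compared (section 2.6): 4 × 3/2 = 6 contrasts per outcome. If Bonferroni is applied over these six, the level is 0.05/6 = 0.0083.
- The only numeric retest correlation given is 0.61 over 12 months, for the AAQ-II (section 2.5.2).

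**Assumptions:** two-sided alpha 0.05; normal scores with equal SD at both times; correlation r = 0.5 or 0.61; a change d of 0.2 to 0.5 SD common to both arms; no VR effect.

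**Step 1. Common change.** The paired t statistic has noncentrality d√n / √(2(1 − r)) with n − 1 degrees of freedom. For n = 22 and r = 0.5 the denominator is 1, so d = 0.3 gives 0.3 × 4.690 = 1.407 and d = 0.5 gives 2.345.

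| n | r | d | Significant at 0.05 | At 0.05/6 |
|---|---|---|---|---|
| 22 | 0.5 | 0 | 5% | 0.8% |
| 22 | 0.5 | 0.2 | 15% | 4% |
| 22 | 0.5 | 0.3 | 27% | 9% |
| 22 | 0.5 | 0.5 | 61% | 31% |
| 32 | 0.5 | 0.3 | 38% | 15% |
| 32 | 0.5 | 0.5 | 78% | 51% |
| 32 | 0.61 | 0.3 | 46% | 21% |
| 32 | 0.61 | 0.5 | 87% | 65% |

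The rows with 32 are closer to the stated intention-to-treat approach. Bonferroni lowers the rates but does not restore the nominal level, because it adjusts for the count of contrasts and leaves the bias in place.

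**Step 2. Regression to the mean on the selection scale.** People selected above a screening cut-off were simulated with no treatment effect and with T0 and T1 measured afresh. The model was a stable trait plus state error, equal lags, a cut 1 to 1.5 SD above the mean, and n = 22.
- No autocorrelation in the error: the T0 to T1 change is zero and the contrast keeps its 5%. The whole drop falls between screening and T0.
- Autocorrelation 0.5 to 0.7, reliability 0.55: a fall of 0.14 to 0.22 SD in population units (0.23 to 0.31 in units of the selected group's SD). The contrast is significant for improvement in 22% to 35% of trials, or 7% to 14% at 0.05/6.
- Same autocorrelation, reliability 0.90: 8% to 12% of trials, or 2% to 3% at 0.05/6.

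**Step 3. The randomised comparison under the same conditions.** In a separate selection simulation with 32 per arm, the between-arm test of T0 to T1 change rejected in 4.4% to 5.2% of trials in every scenario. In the Step 2 runs, with 22 per arm, it also stayed at about 5%.

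**Step 4. SCOFF across section 2.6.**

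| Analysis | SCOFF listed? |
|---|---|
| VR-arm contrasts | Yes |
| Between-arm ANOVA | No |
| MANOVA, five dependent variables | No |
| MANCOVA, opening sentence | Yes |
| MANCOVA, five-variable specification | No |

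**Step 5. Comparator at follow-up.** Section 2.3 offers controls the VR intervention once the study is concluded. Section 2.4.2 offers it after six weeks, which is before T2 and T3. The two statements cannot both hold.

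**The case against.** The strongest reply is that the randomised comparison is planned and carries the efficacy claim. Section 2.6 keeps the word efficacy for the time-by-group ANOVA, adds MANOVAs and T0-adjusted MANCOVAs, and section 2.2 sizes the trial on a two-group repeated-measures ANOVA. The Abstract states the expected result as improvement compared with controls. All of this stands, and it limits the point to labelling.

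A reader might infer that a significant VR-arm change with a null between-arm test would count as success. The documents state no such rule. The phrase in the Introduction can equally be read as requiring the control comparison.

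A reader might also infer that selection on high scores guarantees a fall after T0. It does not. T0 is re-measured after screening, so regression to the mean persists beyond T0 only if the error in the screening score is autocorrelated. It also acts directly only on the scale used for selection. DERS-16, AAQ-II, MPFI-EA and the DASS-21 stress scale are not selection scales. The 0.55 used in Step 2 is the FTND's internal consistency, not a retest reliability, and section 2.5.1 gives at least 0.90 for the EDE-Q global score. Those rates should not be carried over to all three samples.

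Finally, it would be wrong to say that SCOFF is never compared between arms, since the opening MANCOVA sentence includes it. The defect is an inconsistent list.

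**Conclusion.** The point holds as a labelling fault that should be corrected. Section 2.6 names an uncontrolled contrast as the test of VR's effects, and change common to both arms would pass as an effect. Under an assumed common change of 0.3 to 0.5 SD and correlation 0.5, a 22-person contrast is significant in about 27% to 61% of trials with no VR effect. The common change and the correlation are assumptions, since the protocol supplies neither for this setting. The direction of the bias rests on neither. Regression to the mean is a conditional and weaker contributor.

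The validity of the planned between-arm analyses at T1 is untouched. At T2 and T3 it depends on settling when controls are offered VR. If they can receive it before those visits, there is no untreated comparator there, and claims of maintained benefit would lean on the VR-arm contrasts.

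**What to change.** 1. In section 2.6, remove the purpose clause about testing the intervention's effects from the VR-arm sentence. Call these contrasts descriptive, and report mean change with a confidence interval for the VR and waiting-list arms in the same table.
2. State that every claim of effect rests on the planned between-arm comparisons, with each time contrast expressed as a group-by-time difference in change. Word the hypothesis in the Introduction to match.
3. Make the SCOFF lists agree: either include it in the between-arm ANOVA, the MANOVA and the MANCOVA specification, or drop it throughout.
4. Reconcile sections 2.3 and 2.4.2 on when controls are offered VR, and say what the T2 and T3 comparison then estimates.

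Items 1 to 3 cost wording and table layout, with no added participants or data. The trial gives up only an uncontrolled claim. Item 4 is a clarification that the T2 and T3 comparisons need in any case.

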### 2.2. Participants and Sample Size

Individuals from the general population (age range: 18–60 years) exhibiting unhealthy lifestyles and behaviors (i.e., heavy smoking, heavy drinking, and dysfunctional eating behaviors) and are at risk for nicotine dependence, alcohol abuse, or eating disorders will be recruited via social media by filling an online battery of self-report psychometric questionnaires (administered via the Qualtrics online platform).

The inclusion criteria will include the following: (a) being between 18 and 60 years of age; (b) having no prior diagnosis according to the DSM-5-TR [33] diagnostic criteria; (c) displaying one of the unhealthy lifestyles and behaviors mentioned above according to the relative screening questionnaires (see Screening measures below).

The exclusion criteria will include the following: (a) lack of capacity to consent for research; (b) current or former diagnosis of psychiatric disorders according to the DSM-5-TR diagnostic criteria; (c) using medical devices (e.g., pacemaker and hearing aids) or having a medical condition (e.g., vertigo and vision impairments) that may interfere with VR technologies; (d) having concurrent physical health conditions that might better explain the presence of these unhealthy behaviors.

Participants will be enrolled until reaching a number of around 64 individuals for each of these three separate samples: (1) individuals who engage in heavy smoking, (2) individuals who engage in heavy drinking, and (3) individuals who report dysfunctional eating behaviors. The sample size was calculated using G*Power [34] and considering our main statistical analyses (repeated measure ANOVAs with a medium effect size of 0.25, power of 0.80, two groups, and four time measurements), with an addition of an estimated 30% drop-out rate.

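### The main efficacy ANOVA uses T0 as an outcome level and not as a covariate: it is valid, but for a sustained benefit it is less powerful than a single T0-adjusted contrast

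*Protocol article*

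**What the plan says.** Protocol article, section 2.2, sizes each of the three samples by "considering our main statistical analyses (repeated measure ANOVAs with a medium effect size of 0.25, power of 0.80, two groups, and four time measurements". The target is "around 64 individuals for each of these three separate samples", "with an addition of an estimated 30% drop-out rate".

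Section 2.6 assesses efficacy against the waiting list, for the behaviour score, each transdiagnostic score and stress, with "repeated measure ANOVAs using time (T0, T1, T2, and T3) as a within-subject factor" and group as the between-subject factor. It does not say whether the group-by-time interaction or the group main effect carries the conclusion. Because it speaks of changes compared between arms, the interaction is the more natural reading.

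The same section then adds repeated-measures MANOVAs and three MANCOVAs per sample, at T1, T2 and T3. Each MANCOVA has five dependent variables, with "scores at T0 and age as covariates". Baseline adjustment is therefore planned, but only in these additional multivariate analyses. No single-outcome comparison between arms adjusts for T0.

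**The concern.** T0 is measured before any treatment, so no treatment effect can exist there. Entering it as a fourth level of time has two consequences.

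- **Group-by-time.** The test is an omnibus test on 3 degrees of freedom. It spreads a sustained benefit over three contrasts and uses T0 only through unadjusted change. A significant result does not say at which visit, or in which direction, the arms differ.
- **Group main effect.** If this were the test, the effect would be averaged over four visits, one of which is null, and so diluted by a quarter.

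At stake is precision in samples of about 45 completers each, when the score needed to recover it is already collected on everyone for every outcome.

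**Working it through.** **The plan's own figure.** After 30% dropout, 64 leaves 64 × 0.7 = 44.8, about 45; if the allowance was applied as a multiplier, 64/1.3 = 49. With f = 0.25, power 0.80, two groups, four times and an assumed alpha of 0.05, the noncentral F needs these totals before dropout:

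- at r = 0.5: 24 for the interaction, 82 for the between-group effect;
- at r = 0: 46 for the interaction (46/0.7 gives 66);
- at r = 0.1: 44 for the between-group effect (44/0.7 gives 63).

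The article states neither r, nor alpha, nor which effect f refers to. So 64 is neither confirmed nor shown wrong. Values near it appear only with r of about 0 to 0.1.

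**Inputs for the comparison.** 45 completers, n = 22.5 per arm (1:1 assumed); SD 1; a benefit pattern (0, d, d, d) over T0 to T3 with d = 0.5 (assumed); compound symmetry with correlation r (assumed 0.3, 0.5, 0.61, 0.7); two-sided 5% (assumed). The value 0.61 is the 12-month retest figure that section 2.5.2 gives for the AAQ-II. It is not a design input.

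**Noncentrality parameters.**

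- Group-by-time, df 3 and 129: λ = (n/2)(0.75d²)/(1−r)
- Unadjusted change contrast (mean of T1–T3 minus T0), df 1 and 43: λ = (n/2)d²/[(1+2r)/3 + 1 − 2r]
- The same contrast adjusted for T0, df 1 and 42: λ = (n/2)d²/[(1+2r)/3 − r²]
- Group main effect, df 1 and 43: λ = (n/2)(0.75d)²/[(1+3r)/4]

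The bracket in the second line equals 4(1−r)/3, so the first two λ are identical. The step between them is purely a matter of degrees of freedom. The step from the second to the third is purely adjustment for T0.

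**Example at r = 0.5.** (n/2)d² = 11.25 × 0.25 = 2.8125.

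- Interaction and unadjusted change: 2.8125 × 0.75/0.5 = 4.22
- Adjusted: 2.8125/(0.6667 − 0.25) = 6.75
- Main effect: 2.8125 × 0.5625/0.625 = 2.53

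| Power, d = 0.5, 45 completers | r = 0.3 | 0.5 | 0.61 | 0.7 |
|---|---|---|---|---|
| Group-by-time, 3 df | 27% | 37% | 46% | 58% |
| Change contrast, 1 df, unadjusted | 40% | 52% | 62% | 74% |
| Same contrast, T0-adjusted | 69% | 72% | 77% | 84% |
| Points due to degrees of freedom | 13 | 15 | 16 | 16 |
| Points due to T0 adjustment | 29 | 20 | 15 | 10 |
| Group main effect | 43% | 34% | 31% | 29% |

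A simulation at r = 0.5 with 23 per arm gave 37% for the interaction and 72% for the adjusted contrast, with type I error of 5.2% and 5.3%.

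**T1 alone.** Adjustment changes the variance factor from 2(1−r) to 1−r². The ratio is (1+r)/2, a fall of 35/25/20/15%. Power rises from 28/37/46/56% to 40/47/54/63%.

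**No dropout (32 per arm), d = 0.5.** The interaction has 51% at r = 0.5 and 75% at r = 0.7; the adjusted contrast has 86% and 94%.

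**Larger effect.** If f = 0.25 is read as the interaction effect, the pattern (0, d, d, d) gives f² = 0.75d²/16, so d = 0.25 × √(16/0.75) = 1.155. At r = 0.5 and 45 completers the interaction λ is 11.25 × 0.75 × 1.334/0.5 = 22.5. Power is 98%, against practically 100% for the adjusted contrast. At r = 0.1 and 22 per arm it is still only 84% against 100%.

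**The case against.** The strongest reply has four parts.

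1. **The ANOVA is valid and nothing is misstated.** This stands. The simulated type I error is nominal, and the point is one of efficiency.
2. **The plan already adjusts for T0 and age at each visit, in the MANCOVAs.** This is partly right. It shows that the authors accept the principle, and the MANCOVAs compare the arms visit by visit. But they test five outcomes jointly and are additional, so the main single-outcome test still goes without adjustment.
3. **A reader might infer that using T0 as an outcome level halves the power.** The documents do not support that as a general statement. The ratio of interaction to adjusted power is 0.39, 0.51, 0.60 and 0.69 across the four correlations. A halving appears only near r = 0.5 with a modest effect. Some 13 to 16 points of each gap come from the 3-df test and not from the handling of T0. With d about 1.15 and r of 0.5 or more there is almost no loss.
4. **The group main effect is probably not the intended test.** This is a fair reading of section 2.6. Its low power matters only if the sponsor meant it to carry the efficacy conclusion, which the article leaves open.

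The gain also depends on the contrast chosen. A T0-adjusted comparison at T1 alone reaches 40/47/54/63%, which is 13/10/8/5 points above the interaction and well short of the figures for the averaged contrast.

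**Conclusion.** The point holds as one of efficiency. The declared main analysis does not use T0 as a covariate and relies on an omnibus test or a diluted main effect. At d = 0.5 and 45 completers, a single T0-adjusted contrast over T1 to T3 raises power from 27/37/46/58% to 69/72/77/84% at r = 0.3/0.5/0.61/0.7. Both the single degree of freedom and the adjustment contribute.

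The size rests on assumed d, r, alpha, 1:1 allocation and compound symmetry, and on a benefit held to T3. That last assumption needs the controls to remain untreated until T3. Sections 2.3 and 2.4.2 differ on when controls are offered the VR intervention, and they must be reconciled before an average over T1 to T3 can be read in this way.

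The documents do not support reading the plan as invalid, as lacking baseline adjustment altogether, or as losing half its power whatever the effect and correlation.

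**What to change.** For each outcome in each sample, make the main between-arm analysis a mixed model with T1, T2 and T3 as the response. Use the T0 score and age as covariates, with group, visit, group-by-visit and T0-by-visit terms. Name the T0-adjusted VR-minus-waiting-list difference averaged over T1 to T3, with its 95% CI, as the lead contrast. Report the differences at T1, T2 and T3 after it. If the sponsor prefers T1 alone as the lead, only the smaller T1 gain should be claimed. Keep the repeated-measures ANOVA as a supportive analysis.

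Confirm that T0 is completed before allocation is disclosed. Section 2.3 places T0 just ahead of the first session, but does not say whether that is before or after randomization.

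The cost is a change of analysis wording, with no extra participants, measurements or software. If T0 currently follows disclosure of allocation, the timing of that questionnaire would also have to change.

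### The only multiplicity correction covers within-group contrasts; the between-arm ANOVAs that test efficacy span five outcomes per sample with no correction and no primary outcome

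*Protocol article*

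**What the plan says.** All references are to the protocol article.

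- **Scope of the correction (2.6):** "To control for Type 1 error in within-group mean contrasts, the Bonferroni correction will be applied". No other adjustment, ordering or gatekeeping is given.
- **Efficacy test (2.6):** the comparison with the waiting list is made by repeated-measures ANOVAs (four times, two groups) on changes "in the relevant unhealthy behavior (FTND, AUDIT, and EDE-Q scores), in transdiagnostic factors (DERS-16, AAQ-II, and MPFI-EA scores), and in stress levels". That is one behaviour measure, three transdiagnostic scores and one stress score: five outcomes.
- **Rank of these ANOVAs (2.2):** "The sample size was calculated using G*Power", and the sentence goes on to identify repeated-measures ANOVAs as the main analyses.
- **Further between-arm models on the same scores (2.6):** "we will perform repeated measures MANOVAs using time (T0, T1, T2, and T3) as a within-subject factor", and "three MANCOVAs will be run (one for T1 scores, one for T2 scores, and one for T3 scores", the latter for each sample.
- **Samples (2.6):** "Data analyses will be performed separately for the three samples that are included in the study".
- **SCOFF:** section 2.5.2 makes it an outcome, "administering the FTND, AUDIT, SCOFF, and EDE-Q at the beginning (T0) and end (T1) of the VR intervention". In 2.6 it appears in the within-group contrasts and in the sentence introducing the MANCOVAs, "relevant unhealthy behavior (FTND, AUDIT, or SCOFF and EDE-Q scores". It is missing from the efficacy ANOVAs and from the five dependent variables listed for both the MANOVA and the MANCOVAs.

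**The concern.** The article decides which tests receive error control and chooses tests that do not bear on efficacy. A fall in a score from T0 to T1 in the VR arm may reflect regression to the mean after selection on a screening cut-off, or simply time. Only the comparison with the waiting list addresses the treatment, and there five results stand side by side with none designated to decide.

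The hypotheses in the Introduction expect benefit on both the behaviours and the transdiagnostic factors, without saying which finding would confirm the intervention. One favourable interaction out of five could therefore be reported as efficacy in that sample. The SCOFF discrepancy adds a smaller uncertainty in the eating sample, because the set of outcomes is not the same from one list to the next.

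**Working it through.** **Inputs.** From the article: five outcomes per sample, four times, two arms, three samples analysed separately, about 64 people per sample, f = 0.25, power 0.80, 30% drop-out. Not in the article and therefore assumed: alpha 0.05 per test, 1:1 allocation, and the correlations between outcomes and between visits.

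**The plan's own figure.** No family-wise error rate is stated; the only figure is the sample size. For the group-by-time interaction, λ = f²·N·m/(1−ρ), with 3 and 3(N−2) degrees of freedom.
- ρ = 0, N = 46: λ = 0.0625 × 46 × 4 = 11.5, power 0.81. Inflated for drop-out, 46/0.70 = 65.7, so 66, close to the stated figure of around 64.
- ρ = 0.5: 24 evaluable (35 with drop-out) would be enough.

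The article states neither ρ nor which effect was sized, so 64 is compatible with a test of one interaction at 0.05 but does not prove it. It shows no allowance for several outcomes.

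**Number of between-arm tests per sample.** 5 ANOVA interactions + 1 MANOVA + 3 MANCOVAs = 9.

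**Family-wise error if tests were independent.** 1 − (1 − 0.05)^k:
- k = 5: 1 − 0.95⁵ = 0.226.
- k = 9: 1 − 0.95⁹ = 0.370. This is only an upper guide, because the models reuse the same scores.

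**Family-wise error with correlated outcomes.** Null data were simulated for five outcomes at four visits. Between-outcome correlation was 0.3 to 0.7. Between-visit correlation was 0.5, with 0.7 also tried at outcome correlations 0.3 and 0.5. Sample sizes were 46 completers and 64 complete cases, with 3,000 to 8,000 trials per setting.

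| What is read as efficacy | Chance of at least one p < 0.05, per sample |
|---|---|
| Any of the five ANOVA interactions | about 15–21% |
| The above, or the MANOVA, or any of the three MANCOVAs | about 25–29% |

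The low end belongs to outcome correlation 0.7 and the high end to 0.3. Results with 46 and with 64 are nearly the same, so the drop-out assumption does not drive them.

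**Why one primary outcome rather than Bonferroni over all five.** At 0.05/5 = 0.01 and ρ = 0, the interaction needs 64 evaluable (64/0.70 = 91.4, so 92 enrolled), and power with 45 completers drops from 0.80 to 0.59. At ρ = 0.5, 34 evaluable (49 enrolled) would do. A single primary outcome keeps 0.05 and avoids this dependence on an unstated correlation.

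**The case against.** **The model family is ranked.** A reader might infer that no test at all is primary and that every between-arm model is an equal route to a claim. The article does not support that. Section 2.2 puts the repeated-measures ANOVAs first, 2.6 ties the efficacy question to them, and the MANOVA and MANCOVAs are introduced as additions. This stands: 15–21% is the main figure, and 25–29% applies only if the added models are also used to claim efficacy. The ranking still leaves five co-equal outcomes.

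**Larger figures can be produced.** Reading ANOVA group main effects as efficacy would raise the per-sample rate to about 36–43%. But 2.6 speaks of differences in change, which is the interaction. Pooling the three samples gives about 39% or more, but only if success in any one sample counts as success. The article treats them as separate populations, separately randomised, sized and analysed, and makes no such claim.

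**Tests at full alpha.** This is an inference, since no alpha is stated. What the text does show is that the correction stops at within-group contrasts.

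**The MANOVA as gatekeeper.** The article does not use it that way. Its power is a separate matter from error control.

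**SCOFF as a sixth efficacy outcome.** The detailed MANOVA and MANCOVA specifications both count five and name EDE-Q alone for eating. This is a list inconsistency to repair, not evidence of a sixth efficacy test.

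**A condensed article may leave hierarchy to a SAP.** Silence would be excusable on that ground. Here the article itself states the scope of the correction and lists the models, and a SAP that followed it would carry the gap forward.

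**Conclusion.** The concern holds in this form: the stated correction protects within-group contrasts, while the five between-arm interactions that carry the efficacy question in each sample have neither a correction nor a primary outcome. At an assumed 0.05 per test, the false-positive chance per sample is three to four times nominal (15/5 = 3; 21/5 ≈ 4) within the declared main analysis alone. The figures rest on the global null, outcome correlations of 0.3–0.7, and the interaction being the effect that is read. The SCOFF inconsistency is real but minor, and does not depend on any assumption about alpha.

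**What to change.** Before any comparison of the arms is seen, amend 2.6 (and 2.5.2 for SCOFF) as follows.

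1. State the alpha. In each sample, name the group-by-time interaction on its own behaviour measure (FTND, AUDIT or EDE-Q global score) as the single confirmatory test. This stays within the repeated-measures analysis on which the sample size was based. Switching to a baseline-adjusted contrast at T1 is possible, but it is a different test from the sized one and is not needed to solve this problem.
2. Treat DERS-16, AAQ-II, MPFI-EA and DASS-21 stress as a secondary family with Holm correction.
3. Label the MANOVA and the three MANCOVAs supportive.
4. Correct across the three samples only if success in any one is to be claimed. With one test per sample the uncorrected rate for that claim would be 1 − 0.95³ = 14.3%.
5. Use EDE-Q in every between-arm model for the eating sample, report SCOFF descriptively, and make the lists in 2.5.2 and 2.6 agree.

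**Cost.** Wording only, with no change to the planned sample size. The secondary outcomes face a stricter threshold: the smallest of the four p-values must fall below 0.05/4 = 0.0125. By the formula above, at f = 0.25 and 45 completers, power for one outcome at that step is about 0.62 if ρ = 0 and 0.95 if ρ = 0.5.
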